### Interventions

Specific interventions of each group are as follows (Figure 2).

**Figure 2 Fig2:**
[figure not shown]
**Locations and stimulation devices. (A)** Points used in the ABVN group and the ABVN plus tone group for transcutaneous electrical nerve stimulation. **(B)** Points used in the non-ABVN plus tone group for transcutaneous electrical nerve stimulation. **(C)** Acupoints used in the electrical acupuncture group. **(D)** Locations of acupoints in the acupuncture group. local acupoints: Tinghui (GB2) and Yifeng (TF17); distal acupoints: Zhongzhu (TE3) and Xiaxi (GB43). **(E)** Innervation of the human auricle, including ABVN (blue grid), great auricular nerve (green grid) and auriculotemporal nerve (red grid) [17]; the black areas show the specific auricular acupoints. TF4, CO10-12, and HX1 are used in the ABVN group and the ABVN plus tone group; HX9 and LO5 are used in the non-ABVN plus tone group. **(F)** Ideograph of sound (tones) stimulus: each speakers is equidistant from the head of the subject.

### ABVN group

All participants will receive transcutaneous electrical stimulation at auricular acupoints innervated by the ABVN. The points are located at the cymba conchae and the triangular fossa, where there is rich ABVN distribution [17]. Main stimulation points according to standard practice include Kidney (CO10), Yidan (CO11), Liver (CO12), and Shenmen (TF4). A transcutaneous electrical nerve stimulator (Suzhou Medical Appliance Co. Ltd., Suzhou, China) will be used in this group. Two carbon-impregnated silicone electrode tips are connected to the transcutaneous electrical nerve stimulator by metal wire; one tip contacts the skin surface points and the other acts as a terminal end in the ear. The stimulation frequency is 20 Hz, the stimulation current is 1 to 5 mA, with stimulus pulses shorter than 1 ms in duration. Each session will last 30 minutes; sessions are performed every other day for 8 weeks.

### ABVN plus tone group

The format will be exactly the same as for the ABVN group. Multiple tones will be delivered by Tinnitus Measurer software (Neonix, USA) at a comfortable listening level during the transcutaneous electrical nerve stimulation. Randomly interleaved pure tones that span the hearing range but exclude the tinnitus tone will be selected. Each session will last 30 minutes; sessions are performed every other day for 8 weeks.

### Non-ABVN plus tone group

The format of this group will be the same as for the ABVN plus tone group, except that the subjects receiving stimulation will be stimulated at auricular acupoints supplied by the great auricular nerve [17]. Each session will last 30 minutes; sessions are performed every other day for 8 weeks.

### Electrical acupuncture group

The subjects of this group will be treated with electrical acupuncture at local and distal points. Acupuncture points are selected as follows. 1. local acupoints: Yifeng (TE17), Tinghui (GB2); 2. distal acupoints: Xiaxi (GB43), Zhongzhu (TE3). Patients will be in a comfortable and relaxed position and asked to concentrate on the treatment task. After the needles are inserted into the acupoints, they will be connected to an electrical point stimulation device (G6805-2A, Shanghai Huayi Medical Instrument CO., Ltd, Shanghai, China) operating at a frequency of 20 Hz and current of 1 to 5 mA, with pulses shorter than 1 ms in duration. The intensity will be adjusted individually based on the tolerance of the patient. All parameters of the electrical stimulation inducing twitching of the muscles indicate effective stimulus. After retaining the needles for 30 min, all needles are taken out using alcohol-soaked cotton balls to avoid infection and bleeding.

The needles (Suzhou Medical Supplies Factory Co., Ltd. Suzhou, China) used in this group are 25 mm in length and 0.3 mm in diameter. Electrical acupuncture is performed by a therapist with rich clinical experience and acupuncture licenses for Chinese medicine practitioners from the Ministry of Health of China. Treatment will be conducted over a period of 8 weeks, at a frequency of every other day.

### Primary outcome measures

The primary outcome is evaluated using the Tinnitus Handicap Inventory, which evaluates 25 items grouped into a functional subscale (11 factors), an emotional subscale (9 factors), and a catastrophic subscale (5 factors). Each question of the Tinnitus Handicap Inventory can be answered by either ‘often’ (4 points), ‘sometimes’ (2 points), or ‘never’ (0 points). The total score allows the tinnitus to be categorized as: ‘slight’ (0 to 16 points), ‘mild’ (18 to 36 points), ‘moderate’ (38 to 56 points), ‘severe’ (58 to 76 points), or ‘catastrophic’ (78 to 100 points). The assessment is at baseline (before randomization), and in the 4th and 8th week, with further follow-up visits after termination of the treatment at the 12th week.

### Secondary outcome measures

A visual analogue scale, measuring the disturbance and the loudness of the tinnitus will be used. This consists of 100 mm lines with ‘0 = total absence’ and ‘100 = maximum’ of tinnitus disturbance and loudness, respectively.

The severity of both anxiety and depression is evaluated using the Hospital Anxiety and Depression Scale, in which seven items for anxiety and another seven items for depression are assessed. Each item is answered by the patients on a four point (0 to 3) response category. A score of 0 to 7 for either subscale could be regarded as being in the normal range, a score of 8 to 10 is just suggestive of the presence of the respective state and a score of 11 or higher indicates the probable presence of the mood disorder [20]. Both of these assessments will be used at baseline (before randomization), and in the 4th and 8th week, with further follow-up visits after termination of the treatment at the 12th week.

### Statistical methods

The trial aims to detect a difference between the four study groups. We present here our power analysis for the primary outcome only. This is deemed a clinically significant difference of a 20-point or greater reduction in score on the Tinnitus Handicap Inventory following treatments. Since this is a novel therapy, we used data from a previous proof-of-concept feasibility study [21], the mean decrease rate is 28% in the VNS group and 0.97% in the control group.

The following formula was used for a four-group trial [22]:$$ {n}_1={n}_2=\frac{{\left({\mu}_{\alpha }+{\mu}_{\beta}\right)}^22P\left(1-P\right)}{{\left({P}_1-{P}_2\right)}^2} $$

Calculations are performed using 80% power and a 5% significance level (two-side). The required sample size is approximately 27 participants for each group. Assuming a 10% dropout rate, we plan to enroll a total of 120 participants with four groups of equal size (30 participants per group).

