### Statistical analysis

In this trial, our primary outcome measure is the Tinnitus Handicap Inventory. We define the treatment response as a reduction in score on the Tinnitus Handicap Inventory following treatments of 20 points or more. First, baseline characteristics will be analyzed using descriptive statistics for each group. Then repeated measures analysis is performed to make comparisons among the treatment groups and the control group (ABVN plus tone versus electrical acupuncture, non-ABVN plus tone versus electrical acupuncture, and ABVN versus electrical acupuncture) at different time points (4th, 8th, and 12th week). If a significant difference is found, the next step is to make comparisons among the three treatment groups in effectiveness. Multiple comparisons will be adjusted according to the Bonferroni correction method. The Kruskal-Wallis test will be employed in the analysis of skewed distribution data. Analysis of variance will be used for numerical variables, and the *χ*^2^ test for categorical variables.

Statistical analysis will be performed by the Medical College of China Three Gorges University, [name]. The statistician is blinded from the allocation of groups. The SPSS 15.0 software package (SPSS Inc., Chicago, IL, USA) will be used to analyze the data.

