Vagal nerve stimulation was developed based on this growing understanding of tinnitus. It may work by activating the nucleus of the solitary tract, which, in turn, may activate the locus coeruleus and nucleus basalis, which release neuromodulators that have significant effects on learning and memory and in plasticity regulation by modulating neurons in the cortex, hippocampus, and amygdala [26]. Engineer and colleagues [8] have indicated that cervical VNS paired with specific auditory stimuli completely eliminated the physiological and behavioral correlates of the phantom sound. They observed that pairing tones with VNS significantly acutely increased excitability and suppressed spontaneous multi-unit activity in rat auditory cortex [37]. Indeed, beneficial effects in relieving psychological symptoms have been confirmed in patients with tinnitus using invasive VNS pairing tones [21] or transcutaneous VNS paired with tones [19,38] in recent small sample pilot studies. However, another experiment also demonstrated that VNS-directed long-lasting reversal of pathological neural plasticity is driven by the repeated association of VNS with tones, and not by VNS alone [8]. German researchers [14] claimed that no clinically relevant improvement of tinnitus complaints was observed after transcutaneous VNS alone. To some extent, this may confirm the suggestion that stimulation at ABVN might prove less effective than VNS because fibers from the auricular branch do not primarily target the nucleus of the solitary tract and so only target it partly. Otherwise, as these researchers themselves suggested [14], the most probable explanation is that VNS alone is not effective in reducing tinnitus, which is supported by the work of Engineer *et al*. [8]. While sound stimulus alone, as a common sensory exposure treatment strategy, has been applied to treat tinnitus for many years [39,40], studies have indicated that it has only provided some temporary relief [41,42]. Therefore, to identify whether ABVN or the combination of ABVN and sound stimulus plays a more important role in relieving tinnitus, we designed this four-armed novel trial to determine their specific effect on tinnitus.

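### The sample size enters mean decreases of 28% and 0.97% as responder proportions, so the stated 80% power is unsupported; whether 27 per group is too few cannot be determined

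*Protocol article*

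**What the plan says.** All references are to the protocol article.

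- **Target effect (Statistical methods).** "This is deemed a clinically significant difference of a 20-point or greater reduction in score on the Tinnitus Handicap Inventory following treatments". Statistical analysis uses the same 20-point threshold to define treatment response.
- **Inputs (Statistical methods).** "we used data from a previous proof-of-concept feasibility study [21"], where "the mean decrease rate is 28% in the VNS group and 0.97% in the control group".
- **Formula (Statistical methods).** n per group = (u_α + u_β)² · 2P(1−P) / (P1−P2)². It is introduced as suited to four groups, but it compares two proportions.
- **Error rates and result (Statistical methods).** "Calculations are performed using 80% power and a 5% significance level (two-side"). The result is about 27 per group, raised to 30 for 10% dropout, 120 in total.
- **Planned analysis (Statistical analysis).** "Then repeated measures analysis is performed to make comparisons among the treatment groups and the control group". Three contrasts against electrical acupuncture are listed, at weeks 4, 8 and 12. Comparisons among the other three groups follow if a difference is found. Multiple comparisons are to be Bonferroni-adjusted.
- **Nature of the source (Discussion).** The feasibility study is listed among studies "using invasive VNS pairing tones [21] or transcutaneous VNS paired with tones [19,38] in recent small sample pilot studies".

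**The concern.** A two-proportion formula needs the fraction of patients in each arm who meet a yes/no criterion, here a THI fall of at least 20 points. The plan supplies figures that it calls mean decreases. The mean of a score change and the proportion passing a threshold are different quantities. One converts to the other only with a baseline level, an SD and a distribution, and the article gives none of these. The formula's variance term, P(1−P), is that of a yes/no outcome and cannot stand in for the variance of THI change, which the repeated measures analysis would need.

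There is a second mismatch. The calculation covers one two-group comparison at 5%, while the analysis section plans three contrasts against an active comparator with a Bonferroni correction.

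This paragraph is the article's only justification of the trial's size. A reader of a null result would take from it that the trial had an 80% chance of detecting the difference of interest, and the calculation does not show that.

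**Working it through.** **1. Reproduce the plan's figure.** Inputs from Statistical methods: P1 = 0.28, P2 = 0.0097, two-sided 5%, 80% power.

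- P = (0.28 + 0.0097)/2 = 0.14485, and 2P(1−P) = 0.2477
- (P1−P2)² = 0.2703² = 0.07306
- (1.960 + 0.842)² = 7.849
- n = 7.849 × 0.2477 / 0.07306 = 26.6, so 27
- 27/0.9 = 30, and 30 × 4 = 120

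The arithmetic is right, and the match shows that the mean decreases were entered as proportions.

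**2. Could the inputs be responder proportions after all?** The text calls them means. Also, 1/0.0097 = 103, so a true proportion of 0.97% needs about 103 controls for a single responder. That does not fit a study the Discussion groups with small pilots. The source itself was not consulted.

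**3. What the formula assumes if the figures are read as means.** √(P(1−P)) = √0.1239 = 0.352, an implicit SD of about 35 percentage points. A difference of 27.03 percentage points at 80% power and two-sided 5% needs:

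| Assumed SD of percentage change | n per group |
|---|---|
| 25 | 14 |
| 30 | 20 |
| 35 | 27 |
| 40 | 35 |
| 50 | 54 |

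So 27 is right only if the SD happens to be about 35. The article offers no value.

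**4. Multiplicity, with both rates accepted.** Power = Φ[0.2703 × √(27/0.2477) − z] = Φ(2.822 − z).

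- 5%: z = 1.960, power 81%
- 0.05/3 = 1.67% (three contrasts against control): z = 2.394, power 67%; n for 80% power is 35.5, so 36
- 0.05/6 (all six pairs): z = 2.638, power 57%; n is 41.1, so 42

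The article does not give the Bonferroni divisor; three is taken here from the listed contrasts.

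**5. Responder endpoint, illustrative only.** Assume that change is normal, that mean falls are 28% and 0.97% of baseline B, and that the SD is s points. The responder rates are then 1 − Φ[(20 − 0.28B)/s] and 1 − Φ[(20 − 0.0097B)/s].

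- B = 40, s = 20: 33% versus 16%, about 105 per group, power at 27 about 29%
- B = 60, s = 15: 42% versus 10%, about 30 per group, power about 76%
- B = 80, s = 10: 60% versus 3%, about 10 per group, power about 99%

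Over B = 40 to 80 and s = 10 to 20, the need is about 10 to 105 per group, on both sides of 27.

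**6. The score itself.** Two-sample t-test on THI change at one time point, 27 evaluable per group, noncentral t:

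| | 5% | 1.67% |
|---|---|---|
| Standardised difference at 80% power | 0.78 | 0.91 |
| In points, SD 20 | 15.5 | 18.1 |
| Power for 20 points, SD 20 | 95% | 88% |
| Power for 20 points, SD 25 | 82% | 68% |

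The SDs are assumptions.

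**The case against.** The strongest reply is that the trial may be adequately sized. If 20 points is read as a between-group difference in mean change, 27 per group gives 82% to 95% power at 5% for SDs of 25 and 20. This stands, and it rules out several stronger readings that a reader might infer.

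- **That the trial has about half the power claimed.** This follows only from selected baselines and SDs. Other equally assumed values give 99%.
- **That a corrected power must be less favourable.** For 20 points at 5% it could be higher than 80%.
- **That a 28% fall contradicts the 20-point criterion because the two agree only at a baseline of 20/0.28 = 71.** If 20 points is a threshold for individual patients, the mean fall need not equal it.
- **That no contrast in this trial could resemble 28% versus 0.97%.** The comparator is active, but the Discussion reports conflicting evidence on acupuncture for tinnitus, so its response is unknown, not known to be high. The Discussion's remark that "stimulation at ABVN might prove less effective than VNS" concerns stimulation alone and does not bear on the paired-tone arm.

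It can also be said that a two-proportion formula is not foreign to the plan, since response is defined as yes/no and a χ² test is listed for categorical variables. That is fair: for a responder comparison the defect lies in the inputs, not the formula.

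None of this rescues the printed calculation, because no reading turns the two means into rates of a 20-point response. Nor does the article format excuse it: formula, inputs and result are all printed, and they do not fit together.

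**Conclusion.** The point holds as an invalid-input error. The figure of 27 is correct arithmetic on quantities the formula does not accept, so the 80% power is unsupported for the responder definition and for the repeated measures analysis alike. Separately, the calculation ignores the planned Bonferroni correction. On the plan's own rates and three contrasts, this alone takes power at 27 from 81% to 67%.

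The documents do not support the conclusion that the trial is too small. That would need the SD of THI change, the baseline THI and the comparator's response, none of which is given. The figures for the score rest on an assumed SD and a single-time-point t-test. A repeated measures model would depend further on the within-patient correlation, which is also not stated.

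**What to change.** In Statistical methods, withdraw the two-proportion calculation and the 80% claim. Keep 30 per group and replace the claim with a statement of what that number can detect:

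- Name the variable and one time point: change in THI total score from baseline, for example at week 8, the end of treatment.
- State the alpha actually used. If the Bonferroni correction covers the three contrasts against electrical acupuncture, this is 1.67%. If it also covers the comparisons among the other three groups, state that divisor.
- With 27 evaluable per group, report 80% power for a standardised difference of 0.78 (5%) or 0.91 (1.67%). At an assumed SD of 20 this is 15.5 or 18.1 points.
- Give power for the 20-point difference over a range of SDs: 95% or 88% at SD 20, and 82% or 68% at SD 25.
- Say that the SD is an assumption and that the response to the active comparator is unknown.

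The cost is rewording one paragraph, with no added patients. The stated power may turn out more or less favourable than 80%.

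### The sample size is powered at an undivided 5% for one two-group test, but the analysis plans three control comparisons plus follow-ups under an undefined Bonferroni family, so 80% power and 5% error cannot both hold

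*Protocol article*

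**What the plan says.** Under Statistical methods, the protocol article gives a formula that solves for n1 = n2 from two proportions and introduces it with "The following formula was used for a four-group trial". The inputs come from an earlier feasibility study: "the mean decrease rate is 28% in the VNS group and 0.97% in the control group". On error rates it says "Calculations are performed using 80% power and a 5% significance level (two-side". The results are "The required sample size is approximately 27 participants for each group" and, after a 10% dropout allowance, 30 per group and 120 in total.

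Under Statistical analysis, a repeated measures analysis compares each of the three ear-stimulation arms with electrical acupuncture "at different time points (4th, 8th, and 12th week". If a significant difference is found, the three ear-stimulation arms are then compared with one another. The section adds: "Multiple comparisons will be adjusted according to the Bonferroni correction method". It does not say which comparisons the correction covers, how many there are, or whether visits count. Neither section names a primary visit or a primary contrast.

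**The concern.** The significance level used for sizing and the level used for testing do not match. The calculation protects one comparison at 5%. The analysis lists at least three between-group comparisons and announces a correction whose scope is open.

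Two things could be lost, depending on that scope. If the correction applies to the three control comparisons, each is tested below 5% and has less power than stated. If it does not, each keeps its power but the chance of at least one false positive among them exceeds 5%. In both cases a reader who takes 80% power and a controlled 5% error rate from the article is misled about one of the two. The Background promises a conclusive answer. At 67% power, a real effect of the assumed size would be missed about one time in three per contrast.

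**Working it through.** **Inputs (Statistical methods):** P1 = 0.28, P2 = 0.0097, two-sided alpha 0.05, power 80%, dropout 10%.

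**Reproducing the plan's figure.** Pooled P = (0.28 + 0.0097)/2 = 0.14485, so 2P(1−P) = 0.24774. The difference is 0.2703, squared 0.07306.

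n = (1.960 + 0.842)² × 0.24774 / 0.07306 = 26.6, rounded up to 27. Then 27/0.9 = 30 per group, and 4 × 30 = 120. The stated figures reproduce, with alpha not divided by anything.

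**Reading A: Bonferroni covers the control comparisons.** Inverting the same formula gives power = Φ(0.2703 × √(27/0.24774) − z) = Φ(2.822 − z), where z is the two-sided critical value.

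| Level | z | Power, 27 per group | Evaluable per group for 80% |
|---|---|---|---|
| 0.05 | 1.960 | 80.6% | 27 |
| 0.05/3 (three control comparisons) | 2.394 | 66.6% | 36 |
| 0.05/6 (plus three follow-ups) | 2.638 | 57.3% | 42 |
| 0.05/9 (three comparisons × three visits) | 2.773 | 52.0% | 45 |

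The 0.05/3 row is the mildest level that corrects the control comparisons at all. With all 30 per group evaluable it gives 72%.

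*Dependence on the test.* About 27 × 0.0097 = 0.26 responders are expected in a control arm, so the normal approximation is weak. Exact enumeration of the uncorrected chi-square test at 0.05/3 gives 73% with 27 per group and 81% with 30 and no dropout. Fisher's exact test gives 58% and 69%.

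*On a mean-score scale.* The large-sample difference detectable with 80% power at 0.05/3 and 27 per group is (2.394 + 0.842) × √(2/27) = 0.88 SD. Using the t distribution it is about 0.91 SD.

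**Reading B: Bonferroni covers only the second step.** Each control comparison is tested at 5% and keeps about 80% power. Three such tests have a family-wise error of 1 − 0.95³ = 14.3% if independent. They share the acupuncture arm, and simulation with 27 per arm gives about 12% at a single visit.

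**Visits.** If Bonferroni covers the three control comparisons but each visit is tested separately at 0.05/3, simulated family-wise error over three visits is about 9 to 11% (between-visit correlation 0.8 down to 0.5). With one visit it is 4 to 5%. This applies only if visits are tested separately.

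**The case against.** The sample-size arithmetic is correct for what it calculates. The fault is a mismatch between two sections, not a slip in computation.

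The Bonferroni sentence directly follows the conditional second step and can fairly be read as covering only that step. A reader might infer that the stated 80% is simply not delivered. The text does not support that as a fact: on this reading power survives and the cost moves to the error rate. This objection stands, so the point has to be put as a choice between two faults.

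A reader might also infer that success can be claimed at any of three visits, or that testing will be at 0.05/9. The article contains no success rule, and a repeated measures model may be used through one overall group effect or a group-by-time test. The 0.05/6 level likewise pools a conditional second step with the first. These figures are possibilities, not consequences of the text.

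The magnitude is also soft. The inputs are mean percentage decreases entered as if they were responder proportions, while the main analysis is repeated measures on the score. No SD or correlation is given, so the power of that analysis cannot be computed. The limitations paragraph does concede a relatively small sample, but it does not mention the level at which power was set.

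None of this removes the core conflict. For the three listed contrasts, neither Reading A nor Reading B gives both about 80% power per contrast with 27 evaluable and a 5% family-wise error.

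**Conclusion.** The concern holds in this limited form. The formula is a two-group formula at an undivided two-sided 5%, and the planned analysis has more comparisons than it allows for.

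- If the three control comparisons are Bonferroni-corrected, power with 27 evaluable per group is about 67% on the plan's own formula and about 73% by exact chi-square.
- If they are not, power stays near 80% but family-wise error is about 12% at one visit.

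The 57% and 52% figures, and the 9 to 11% error across visits, are conditional on wider families or on separate tests by visit, which the article leaves open. All power figures except the SD-based one rest on the plan's own proportion inputs, and they move with the choice of test. With no dropout at all, exact chi-square at 0.05/3 would reach 81%, so the shortfall is firm at the planned evaluable number but not at every possible one.

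**What to change.** 1. Name one primary visit, for example week 8 (end of treatment), with the other visits secondary.
2. Name the primary contrasts and state that the multiplicity correction covers them. The Background asks whether ABVN stimulation alone or combined with tones matters more. That comparison now sits only in the conditional second step, so the authors should decide whether it belongs in the primary family. The 67% applies to a family of three.
3. Restate power at the level that will be used. With three contrasts under Bonferroni this is about 67% on the present inputs, or a detectable difference of about 0.91 SD with 27 evaluable per group. Label the percentage as resting on the plan's own proportion inputs.
4. Stop describing the formula as one for four groups.

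Optionally, Holm can replace Bonferroni with the same error control. On the present inputs simulated power per contrast is then about 74% if all three arms are effective. Bonferroni is valid, so this is a preference.

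The cost is a few sentences in the two statistical sections and a lower stated power. No extra patients are needed, and the article reports that recruitment is still under way.
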